# Substitution of ethambutol with linezolid during the intensive phase of treatment of pulmonary tuberculosis: study protocol for a prospective, multicenter, randomized, open-label, phase II trial

**DOI:** 10.1186/s13063-017-1811-0

**Published:** 2017-02-13

**Keywords:** Tuberculosis, Multicenter, Randomized trial, Ethambutol, Linezolid

## Abstract

**Background:**

Linezolid, an oxazolidinone, substantially improves treatment outcomes of multidrug-resistant tuberculosis and extensively drug-resistant tuberculosis. We started a trial to test whether the use of linezolid instead of ethambutol could increase the rate of sputum culture conversion as of 8 weeks of treatment in patients with drug-susceptible tuberculosis.

**Methods/design:**

This is a phase II, multicenter, randomized study with three arms. We are enrolling patients with pulmonary tuberculosis without rifampicin resistance screened by the Xpert MTB/RIF® assay. The standard treatment arm uses isoniazid (6 months), rifampicin (6 months), pyrazinamide (2 months), and ethambutol (2 months). Experimental arm 1 uses linezolid (600 mg/day) for 4 weeks instead of ethambutol. Experimental arm 2 uses linezolid (600 mg/day) for 2 weeks instead of ethambutol. The primary outcome is the sputum culture conversion rate on liquid media after 2 months of treatment. Secondary outcomes include the sputum culture conversion rate on solid media after 2 months of treatment, time to sputum culture conversion on liquid and solid media, cure rate, and treatment success rate. The frequencies of total adverse events (AEs) and serious AEs will be described and documented. Based on an α = 0.05 level of significance, a power of 85%, a 15% difference in the culture conversion rate after 2 months between the control arm and experimental arm 1 (75% vs. 90%), a 10% default (loss to follow-up) rate, and a 10% culture failure, the required number per arm was calculated to be 143 (429 in total).

**Discussion:**

This trial will reveal the effectiveness and safety of 2 or 4 weeks of use of linezolid instead of ethambutol for patients with drug-susceptible pulmonary tuberculosis. If a new regimen including linezolid shows a higher culture conversion rate by week 8, and is safe, it could be tested as a 4-month antituberculosis treatment regimen in the future.

**Trial registration:**

ClincalTrials.gov, NCT01994460. Registered on 13 November 2013.

**Electronic supplementary material:**

The online version of this article (doi:10.1186/s13063-017-1811-0) contains supplementary material, which is available to authorized users.

## Background

Tuberculosis (TB) is a major challenge for the maintenance of human health. In 2014, there were 9.6 million new cases of TB, including 5.4 million men, 3.2 million women, and 1.0 million children. TB killed 1.5 million people in 2014 [1].

The current standard short-course treatment for pulmonary TB requires 6 months to complete. This long treatment duration increases the likelihood of adverse effects while decreasing patients’ adherence to anti-TB drugs. As many as 16.8% of patients with TB who were treated with the 6-month regimen showed poor compliance [2]. Patients with TB who take their medication irregularly could spread TB to others, and/or their condition could progress to drug-resistant TB. A new, shorter duration anti-TB treatment regimen could decrease the frequency of this poor compliance.

Linezolid, an oxazolidinone, exerts antibacterial activity via inhibiting protein synthesis by binding the 23S ribosomal RNA portion of the bacterial 50S ribosomal subunit [3]. Linezolid has shown modest early bactericidal activity against *Mycobacterium tuberculosis* [4, 5]. However, adding linezolid has resulted in a culture conversion rate of 89% by 6 months in patients with extensively drug-resistant TB (XDR-TB) refractory to previous treatment [6].

Considering its impressive anti-TB effect, linezolid could also have additive activity when administered along with existing anti-TB drugs in patients with drug-susceptible pulmonary TB. We hypothesize that the use of linezolid instead of ethambutol will increase the culture conversion rate by week 8.

## Methods/design

### Setting

This randomized controlled trial is to be conducted at four hospitals in South Korea. The flow diagram of the trial is shown in Fig. 1. Three of the hospitals are affiliated with the Seoul National University College of Medicine (Seoul National University Hospital, Seoul National University Bundang Hospital, and Seoul National University Boramae Medical Center), and the other is the National Medical Center in Seoul. All hospitals are located in an urban area.

**Fig. 1 Fig1:**
[figure not shown]
Flow diagram of the trial

### Design

This is a phase II, multicenter, randomized study with three arms. Eligible patients are first screened by safety laboratory testing and using the Xpert MTB/RIF® assay (Cepheid, Sunnyvale, CA, USA) for rifampicin resistance. Patients with TB without resistance to rifampicin are randomized to the following three arms at a 1:1:1 ratio:Arm 1 (control arm): Standard treatment for drug-sensitive pulmonary TB uses isoniazid (6 months), rifampicin (6 months), pyrazinamide (2 months), and ethambutol (2 months) as recommended by the Korean National Guidelines [7] (Table 1).

**Table 1 Tab1:** Dose and schedule of first-line anti-TB drugs recommended by the Korean National Guidelines [7]

Drug	Dosage			Frequency and timing
	Dose/kg	Recommended dose	Maximal dose	
Isoniazid	5 mg/kg	300 mg/day	300 mg/day	Daily, before meal
Rifampicin	10 mg/kg	450 mg (<50 kg)	600 mg/day	Daily, before meal
		600 mg (≥50 kg)		
Pyrazinamide	20–30 mg/kg	1000 mg (<50 kg)		Daily, before or after meal
		1500 mg (50–70 kg)		
		2000 mg (>70 kg)		
Ethambutol	15–20 mg/kg	800 mg (<60 kg)		Daily, before or after meal
		1200 mg (60–80 kg)		
		1600 mg (>80 kg)		Arm 2 (experimental arm 1): Treatment using isoniazid (6 months), rifampicin (6 months), pyrazinamide (2 months), and linezolid is used (600 mg/day, 4 weeks).Arm 3 (experimental arm 2): Treatment using isoniazid (6 months), rifampicin (6 months), pyrazinamide (2 months), and linezolid is used (600 mg/day, 2 weeks).

The study timeline is shown in Table 2. Returned trial product is reconciled at every visit by the research nurse to ensure adherence to the allocated regimen. If a participant misses a scheduled visit, the research nurse makes immediate phone contact. The duty physician makes a decision on discontinuation or modification of the allocated regimen for patients showing clinical deterioration or reporting adverse events associated with the anti-TB treatment. No treatment or intervention is prohibited for the participants, and any ancillary and/or post-trial care is determined by the duty physician.

**Table 2 Tab2:** Study timeline

Visit	Screening	Baseline visit^a^	Treatment							
Visit number	1	2	3	4	5	6	7	8	9	10
Weeks (w)	−2 w to −1 d	0	1 w	2 w	4 w	8 w	12 w	16 w	20 w	24 w
Visit window	NA	NA	±4 d	±4 d	±1 w	±2 w	±2 w	±2 w	±2 w	±2 w
Consent	X									
Randomization		X								
Medical history	X									
Physical examination	X		X	X	X	X	X	X	X	X
Neurologic examination	X		X	X	X	X	X	X	X	X
Xpert MTB/RIF® assay	X									
Sputum AFB smear	X	X^d^	X	X	X	X	X	X	X	X
TB culture (solid)	X	X^d^	X	X	X	X	X	X	X	X
TB culture (liquid)	X	X^d^	X	X	X	X	X	X	X	X
DST^b^	With first cultured *Mycobacterium tuberculosis*									
CXR	X	X^d^			X	X	X	X	X	X
HIV, HBV	X									
Total bilirubin, AST/ALT, creatinine	X	X^d^	X	X	X	X	X	X	X	X
Complete blood count	X	X^d^	X	X	X	X	X	X	X	X
Optic test		X	X	X	X	X				
Urine HCG^c^	X									
Compliance of drug intake			X	X	X	X	X	X	X	X
Adverse drug reaction			X	X	X	X	X	X	X	X
Other medications^e^		X	X	X	X	X	X	X	X	X

*w* weeks, *d* days, *NA* not applicable, *AFB* acid-fast bacilli, *TB* tuberculosis, *DST* drug susceptibility test, *CXR* simple chest radiography, *HIV* human immunodeficiency virus, *HBV* hepatitis B virus, *AST* aspartate transaminase, *ALT* alanine transaminase, *HCG* human chorionic gonadotropin

^a^Treatment will be initiated at the baseline visit, as TB treatment should be started promptly following diagnosis

^b^Drug susceptibility test for isoniazid, rifampicin, ethambutol, pyrazinamide, streptomycin, kanamycin, amikacin, capreomycin, ofloxacin, levofloxacin, moxifloxacin, prothionamide, cycloserine, and *para*-aminosalicylic acid

^c^Only in females of childbearing potential

^d^Can be omitted if the results of previous tests within the prior 4 weeks are available

^e^In particular, immunosuppressive agents (including corticosteroids)

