### Eligibility criteria for participants

Participants with pulmonary TB satisfying the inclusion criteria are enrolled competitively by investigators in the outpatient clinic as well as the inpatient setting in the four participating hospitals. The inclusion criteria are as follows: men and women aged from 20 to 80 years, with documented sputum Xpert MTB/RIF® assay-positive pulmonary TB at screening, and administration of current TB therapy (if any) for ≤7 days at the time of enrollment.

Patients will be excluded if they have HIV/AIDS. Female patients of childbearing potential who are pregnant, breastfeeding, or unwilling to avoid pregnancy will also be excluded. Additionally, any of the following factors will lead to exclusion: (1) absolute neutrophil count of <2000 cells/mL, (2) white blood cell count of <3.0 × 10^3^/μL, (3) hemoglobin levels of <7.0 g/dL, (4) serum creatinine levels of >2.0 mg/dL, (5) aspartate aminotransferase levels of >100 IU/L, (6) alanine aminotransferase levels of >100 IU/L, (7) total bilirubin levels of >2.0 mg/dL, (8) history of optic neuritis or peripheral neuropathy, and (9) other significant laboratory abnormalities (i.e., absolute neutrophil count, creatinine levels). Finally, we also exclude patients with the need for ongoing therapy with selective serotonin reuptake inhibitors, tricyclic antidepressants, serotonin 5-hydroxytrptamine 1 receptor agonists (triptans), meperidine, buspirone, monoamine oxidase inhibitors, sympathomimetic agents (e.g., pseudoephedrine), vasopressive agents (e.g., epinephrine, norepinephrine), or dopaminergic agents (e.g., dopamine, dobutamine).

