### Statistical analysis

The results of this trial will be analyzed based primarily on the intention-to-treat (ITT) approach. In addition, a per protocol analysis will be performed secondarily. A safety analysis will be performed based on the safety group. The ITT groups will comprise participants who satisfy the inclusion and exclusion criteria, those who are randomized, and those who take the trial drug at least once. The per protocol groups will comprise participants from ITT satisfying the following conditions: (1) participants took the trial drug (ethambutol or linezolid) at greater than 80% of the planned dose (ethambutol, ≥45 days for control arm; linezolid, ≥23 days for experimental arm 1; linezolid, ≥12 days for experimental arm 2), and (2) participants completed the clinical trial according to the protocol. The safety group includes participants who took the trial drug at least once. No interim analysis of the data is planned.

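### Therapy that would bar a patient at entry may be started during the 2 or 4 weeks of linezolid, because the Design section prohibits nothing after entry

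*Protocol article*

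**What the plan says.** **Entry.** Under Eligibility criteria for participants, the article states: "we also exclude patients with the need for ongoing therapy with selective serotonin reuptake inhibitors, tricyclic antidepressants". The list goes on to triptans, meperidine and buspirone, and ends with "monoamine oxidase inhibitors, sympathomimetic agents (e.g., pseudoephedrine), vasopressive agents (e.g., epinephrine, norepinephrine), or dopaminergic agents (e.g., dopamine, dobutamine". That makes nine drugs or classes. The criterion concerns a need for *ongoing* therapy. It is applied before randomization, so it covers all three arms.

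**After entry.** The Design section states: "No treatment or intervention is prohibited for the participants, and any ancillary and/or post-trial care is determined by the duty physician". The sentence has no exception, no time limit and no limit by arm.

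**Linezolid period.** In experimental arm 1 (arm 2), "linezolid is used (600 mg/day, 4 weeks"; in experimental arm 2 (arm 3), "linezolid is used (600 mg/day, 2 weeks".

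**Related provisions.** Table 2 lists other medications at baseline and at every treatment visit, and its footnote singles out immunosuppressive agents. The Design section lets the duty physician stop or modify the allocated regimen for clinical deterioration or adverse events. The per-protocol set requires a minimum number of days on trial drug ("linezolid, ≥23 days for experimental arm 1; linezolid, ≥12 days for experimental arm 2") and completion according to the protocol.

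**The concern.** An entry criterion based on concomitant therapy usually has a counterpart for the treatment period, because whatever made the combination undesirable at screening does not normally lapse when study drug begins. Here the counterpart is not merely absent. The Design section affirmatively says that nothing is prohibited. This is therefore a stated rule drawn too broadly, not a detail that a condensed article leaves to the full protocol. A restriction in the full protocol would conflict with the published sentence.

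What is at stake is participant safety in the two linezolid arms, on a small scale: the protocol permits, during linezolid, a co-exposure to ongoing therapy that its own entry criterion screens out.

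**Working it through.** No stated figure is in dispute, so the check is mainly a comparison of sections.

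**1. Scope of the two rules.** The eligibility criterion acts once, before randomization, on patients who need ongoing therapy with a listed drug or class. The Design sentence acts on participants, that is, after entry, and covers every treatment. The two never apply at the same moment, so they do not strictly contradict each other. The gap lies between them: ongoing therapy with a listed class is a bar the day before entry and permitted the day after.

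**2. Does any other section close the gap?**

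| Provision | Where | What it does | Restricts a start during linezolid? |
|---|---|---|---|
| Other medications row | Table 2 | Records use at each visit; footnote points to immunosuppressants | No |
| Duty physician's decision on the regimen | Design | Stop or modify for clinical deterioration or adverse events | No; a start of a listed drug is not a named ground |
| Duty physician's decision on ancillary care | Design | Leaves care to clinical judgment | No |
| Documentation of adverse events | Safety assessment | Records events after they occur | No |
| Safety board | Supervision of the trial | Recommends at trial level | No |
| Per-protocol conditions | Statistical analysis | Minimum days on drug; completion per protocol | No; no concomitant-drug condition, and nothing is prohibited that could be breached |

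None does.

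**3. Planned exposure.** Experimental arm 1: 4 weeks × 7 = 28 days. Experimental arm 2: 2 weeks × 7 = 14 days.

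**4. Per-protocol thresholds, needed to cost the fix.** The plan's rule is more than 80% of the planned dose:
- Experimental arm 1: 0.80 × 28 = 22.4, so at least 23 days. This matches the article. Slack: 28 − 23 = 5 days.
- Experimental arm 2: 0.80 × 14 = 11.2, so at least 12 days. This matches the article. Slack: 14 − 12 = 2 days.

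A participant who stops linezolid with more than 5 (or 2) planned days missed leaves the per-protocol set.

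**5. Effect on the primary analysis.** The intention-to-treat set is defined by eligibility, randomization and at least one dose. Concomitant medication plays no part in it, in the chi-square or Fisher's exact test, or in the sample size. Starting a listed drug changes none of these.

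**6. Frequency and harm.** The article gives no rate of starting these drugs, no rate of harm from doing so, and no reason for the exclusion. Neither quantity can be derived.

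**The case against.** The strongest case against the point has four parts.

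- **The criterion says ongoing therapy.** A reader might infer that any use of a listed drug during linezolid is something the entry rule forbids. The text does not support that. A short pseudoephedrine course, a single dose of meperidine or emergency epinephrine is not ongoing therapy and would not by itself have excluded anyone. The inconsistency holds only for therapy of the kind that would have barred entry. This part stands and limits the point.
- **The harm is not in the document.** The criterion is not tied to linezolid and applies equally to the ethambutol arm. The Discussion names peripheral neuropathy and bone marrow suppression as linezolid's serious adverse events and mentions no drug interaction. This also stands: a reader might infer a documented interaction risk, but the article shows only an entry rule without an on-treatment counterpart.
- **A competent physician would manage this anyway.** Discretion, visit-by-visit logging, neurologic examination and an unblinded safety board all exist. They reduce the consequence. They do not make avoidance the default, and the stated grounds for changing the regimen arise only after deterioration or an adverse event.
- **Gaps between visits do not size the problem.** One might count linezolid days between scheduled visits: 28 − 14 = 14 in experimental arm 1 and 14 − 7 = 7 in experimental arm 2. Those figures measure delay in logging. The issue is permission, and the fix would not shorten any gap.

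**Conclusion.** The point holds as a minor participant-safety inconsistency, worth considering. Ongoing therapy with a class that bars entry may be started during 28 or 14 planned days of linezolid without a protocol breach, and no stated provision restricts it.

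Its size in participants or events cannot be given. The primary intention-to-treat comparison and the sample size are unaffected. A reader might go further and call the two sections contradictory; they are not, since one governs entry and the other care after entry.

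The conclusion rests on two assumptions: that the Design sentence means what it says, without an unstated exception, and that whatever reason lay behind the exclusion still applies while linezolid is taken. The article does not state that reason.

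**What to change.** Keep the Design sentence and qualify it along these lines:

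> The exception is that the drug classes listed in the exclusion criteria are not to be started while linezolid is being taken unless clinically necessary. If one is necessary, including emergency vasopressors, it is given without delay and the duty physician decides whether to stop linezolid.

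This makes avoidance the default and gives a ground to stop linezolid before an adverse event occurs. It is slightly wider than the entry criterion because it does not separate short from ongoing use; the clinical-need exception covers necessary short use. That exception must stay, because the list includes epinephrine and norepinephrine and the rule must not delay emergency care.

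**Costs.** No new visit, test or form is needed, but it is an amendment at four hospitals in a trial that has been recruiting since February 2014. The rule binds only the linezolid arms, so an open-label trial would carry an arm-specific rule on concomitant care. A few participants may stop linezolid early. They remain in the intention-to-treat analysis with shorter exposure, and leave the secondary per-protocol set if they fall below 23 days (experimental arm 1) or 12 days (experimental arm 2). No other change is needed.

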### Outcomes

The primary outcome is the proportion of participants with sputum culture conversion on liquid media after 2 months of treatment. Secondary outcomes include the proportion of participants with sputum culture conversion on solid media after 2 months of treatment, the interval from enrollment to sputum culture conversion on liquid and solid media, the proportion of cured participants, and the proportion of participants with a treatment success rate.

### Definitions

#### Culture conversion and rate of culture conversion

We define culture conversion as two consecutive negative sputum cultures on liquid or on solid media. The date of culture conversion is defined as the date of the initial negative culture. Negative sputum cultures followed by contaminated cultures are also regarded as culture conversion. Culture conversion is also defined as a case where the participant cannot expectorate sputum after one negative sputum culture.

#### Treatment outcomes

We define treatment outcomes according to the Korean TB Guidelines as follows [7]:Cure: We define cure as a negative sputum culture after (or during the last months of) treatment combined with one or more prior negative sputum cultures.Treatment completed: We define treatment completed as (1) a negative sputum culture after or at the end of treatment, but without a prior negative sputum culture or (2) a negative sputum culture during treatment, but the lack of a negative sputum culture after or during the last month of treatment.Treatment success: We define treatment success as achievement of a cure or treatment completion.

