#### Assumptions

The sputum culture conversion rate on liquid media after 2 months in patients who are treated at Seoul National University Hospital is approximately 75% [8]. We assume that there will be a 90% culture conversion rate on liquid media after 2 months in experimental arm 1 (primary hypothesis) and a 10% default (loss to follow-up) rate, and that 10% of participants will have a positive Xpert MTB/RIF® assay result but a negative result for *M. tuberculosis* culture.

Based on an α = 0.05 level of significance, a power of 85%, and a 15% difference in the culture conversion rate after 2 months between the control arm and experimental arm 1 (75% vs. 90%), the sample size per arm was calculated to be 114 (342 in total). After consideration of a 10% default rate and 10% culture failure in participants with a positive Xpert MTB/RIF® assay result, the final number per arm was calculated to be 143 (429 in total).

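### As worded, 'treatment success' means at least one negative culture at any time, so participants who default, die, stop or end culture-positive after an early negative count as successes

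*Protocol article*

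**What the plan says.** The article's 'Treatment outcomes' section introduces its definitions with "We define treatment outcomes according to the Korean TB Guidelines as follows" and then writes them out:

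- Cure: "a negative sputum culture after (or during the last months of) treatment combined with one or more prior negative sputum cultures".
- Treatment completed, limb (1): "a negative sputum culture after or at the end of treatment, but without a prior negative sputum culture".
- Treatment completed, limb (2): "a negative sputum culture during treatment, but the lack of a negative sputum culture after or during the last month of treatment".
- Treatment success: "We define treatment success as achievement of a cure or treatment completion".

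The 'Outcomes' section lists "the proportion of cured participants, and the proportion of participants with a treatment success rate" among the secondary outcomes. 'Analysis of secondary outcomes' calls these analyses explorative and compares cure, completion and success rates across the three arms by chi-square or Fisher's exact test. The primary analysis set ('Statistical analysis') is every eligible randomized participant with at least one dose of trial drug, so early leavers stay in the denominator. The sample size 'Assumptions' expect "a 10% default (loss to follow-up) rate". The article does not define failure, default or death as outcomes, and gives no rule that one category takes precedence over another.

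**The concern.** All three routes to success are defined by culture results alone. Limb (2) carries the name 'treatment completed' but has no completion condition. It also speaks of lacking a negative culture at the end, which a positive culture satisfies as well as a missing one. The category can therefore hold participants who plainly did not complete treatment, and some whose final culture was positive.

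Two reported comparisons are affected: the completion rate, which early leavers with one negative culture would raise, and the success rate, in which they would be counted as good outcomes. The Discussion notes that linezolid is often accompanied by serious adverse events, and the Design section lets the duty physician discontinue the allocated regimen. Stopping and default could therefore differ by arm, and such a difference would be muted in these two outcomes.

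**Working it through.** **1. The plan's own figure.** The article gives no expected success rate. The only figure borrowed here is the arm size, and it reproduces: n = [1.96·√(2·0.825·0.175) + 1.036·√(0.75·0.25 + 0.90·0.10)]² / 0.15² = (1.053 + 0.546)² / 0.0225 = 113.7, so 114; 114 / (1 − 0.20) = 142.5, so 143. Ten percent default is 14.3 participants per arm.

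**2. The logic (no assumptions needed).** Let L be a negative culture at the end of treatment and P a negative culture earlier.

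| P | L | Cure (P and L) | Completed (exactly one of P, L) | Success |
|---|---|---|---|---|
| no | no | no | no | no |
| no | yes | no | yes, limb (1) | yes |
| yes | no | no | yes, limb (2) | yes |
| yes | yes | yes | no | yes |

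Success is P or L: at least one negative culture. Moving the boundary between cure and completed does not change this union.

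**3. Who enters through limb (2).** Table 2 schedules cultures at weeks 1, 2, 4, 8, 12, 16, 20 and 24. A participant negative at week 2 and lost at week 3 qualifies. So does one negative at week 4 who dies at week 6, and one negative at week 8 with a positive culture at week 24.

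**4. Size without a model.** If a share s of defaulters had an earlier negative culture, 14.3·s per arm are counted as successes. For s = 25%, 50%, 75% and 100% that is about 4, 7, 11 and 14 participants, or 2.5, 5, 7.5 and 10 percentage points.

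**5. Size with a model.** Assumptions, none from the document except the 10%, the 75% and 90%, and the visit weeks:

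- Clearance is Weibull, F(t) = 1 − (1 − p)^((t/8)^k), with p = 0.75 or 0.90 at week 8 and k = 0.5, 1 or 2.
- Cleared participants stay negative.
- Default is independent of clearance and evenly spread over 24 weeks.

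Then s is the average of F at the last visit attended. For p = 0.75, k = 1:

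s = [1·0.159 + 2·0.293 + 4·(0.500 + 0.750 + 0.875 + 0.938 + 0.969)] / 24 = 16.87 / 24 = 0.703.

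With default confined to the first 8 weeks, s = [1·0.159 + 2·0.293 + 4·0.500] / 8 = 0.343.

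**6. A default difference between arms.** With default rate d, success as written is (1 − d)·F(24) + d·s; with completion required it is (1 − d)·F(24). Going from d = 10% to 20% (default even over 24 weeks), the falls are 0.1·(F(24) − s) and 0.1·F(24). Taking cure as cleared by week 20 and still followed at week 24, cure falls by 0.1·F(20).

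| p | k | s, 24 weeks | counted of 14.3 | s, first 8 weeks | F(24) | Fall as written | Fall, completion required | Fall in cure |
|---|---|---|---|---|---|---|---|---|
| 0.75 | 0.5 | 71.4% | 10.2 | 48.6% | 90.9% | 2.0 | 9.1 | 8.9 |
| 0.75 | 1 | 70.3% | 10.1 | 34.3% | 98.4% | 2.8 | 9.8 | 9.7 |
| 0.75 | 2 | 67.4% | 9.6 | 17.0% | 100.0% | 3.3 | 10.0 | 10.0 |
| 0.90 | 0.5 | 84.3% | 12.1 | 64.2% | 98.1% | 1.4 | 9.8 | 9.7 |
| 0.90 | 1 | 80.3% | 11.5 | 48.3% | 99.9% | 2.0 | 10.0 | 10.0 |
| 0.90 | 2 | 73.5% | 10.5 | 25.7% | 100.0% | 2.7 | 10.0 | 10.0 |

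Falls are in percentage points. Participants who end culture-positive after an earlier negative are not modelled and would add to the count.

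**The case against.** Cure is a separate secondary outcome with its own comparison, and it needs a negative culture at the end. In the last column of the table it falls by 9–10 points, almost the same as a properly defined success rate. Serious adverse events are all documented, grade 3 or 4 events are compared between arms, and compliance is recorded at every treatment visit. A reader might infer that the trial cannot show harm from default or stopping. The document does not support that: success and completion are blunted, but the signal remains elsewhere. This defence holds only if the end of treatment means the end of the planned six months. If it meant the last treatment actually taken, early leavers could also enter cure. The article does not say which.

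The article cites the Korean guideline and labels the category 'treatment completed', so a completion condition or a precedence rule may exist in a source not shown. A reader might infer that the trial will score deaths as successes. What can be shown is that the printed rule does so after an earlier negative culture; intent cannot be judged. The point still stands, because the article prints the definition in full rather than deferring to the source, and what it prints contradicts its label.

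Two further inferences go too far. Not every defaulter or death is counted, only those with an earlier negative culture, and that share depends strongly on when default occurs. Nor is success near its ceiling in every case: at p = 0.75, k = 0.5 it is 0.9·0.909 + 0.1·0.714 = 89% with 10% default and 0.8·0.909 + 0.2·0.714 = 87% with 20%.

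Finally, neither the primary outcome nor the sample size uses treatment success. Nor does the stated basis for going on to a 4-month regimen, which is week-8 conversion and safety. That limits the severity.

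**Conclusion.** The point holds, and should be fixed. It follows from the printed definitions alone that treatment success equals at least one negative culture during or after treatment. Limb (2) thus admits participants who, after an earlier negative, defaulted, died, stopped or ended culture-positive. This distorts both the completion rate and the success rate.

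The size rests on assumptions. With 10% default spread evenly over 24 weeks and the clearance curves above, 67–84% of defaulters (about 10–12 of 143 per arm) are counted as successes. With default in the first 8 weeks the share is 17–64%. A 20% versus 10% default difference, worth 9–10 points, would appear as about 1.4–3.3 points in treatment success under even timing, while the cure rate would still show it if the end of treatment means the planned course.

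The damage is confined to secondary outcomes that the article calls explorative.

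**What to change.** Before analysis, reconcile the definition with its own label and with the cited national guideline:

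- State that 'treatment completed' requires completion of the planned course, and how completion is established from the compliance data.
- State that death, default, early stopping and a positive end-of-treatment culture are separate, mutually exclusive categories, none of which is treatment success.
- Say whether the end of treatment means the end of the planned course or of the treatment actually taken, so that cure and completed use the same reference point.

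The exact wording should come from the guideline, which was not available for this review. Treatment success can remain cure plus completed.

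The cost is one reworded definition and the matching derivation. Table 2 already schedules compliance and cultures at every treatment visit. The only downside is a lower reported success rate.
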